### Procedure for unblinding if needed {24c}

Not applicable, as this is an open-label trial with blinded evaluators where double-blinding to intervention is not possible.

## Data collection and management

### Plans for assessment and collection of outcomes {25a}

All patients will undergo the same set of assessments at baseline, end-of-treatment, and at the 6 months follow-up. The outcome assessments will include dysphagia severity assessed with DOSS [18, 19], and PAS [30] using FEES, nutritional status [23], swallowing-related quality of life [24], rate of aspiration pneumonia, lip force [26], functional status, and health status [27, 28] including death. Data regarding stroke severity and type will be collected. All instruments that will be used have high validity and reliability (see Outcomes section). The investigators conducting the assessments will be trained in how to perform assessment with each instrument. Data collection form is in the protocol and will be added in the REDCap system [31]. The study protocol (paper format) will be stored in a secure room at Umeå University.

### Plans to promote participant retention and complete follow-up {25b}

Several strategies will be used to promote participant retention and complete follow-up. During the follow-up period, participants in both groups will be contacted 1 week after allocation for follow-up on their usual care regarding individualized compensatory strategies. The intervention group will also be followed up regarding their oral neuromuscular training (see “Intervention”) and asked if they have any questions or need assistance with monitoring the training. This keeps the participants in both groups engaged to follow the study procedures, promoting successful retention.

### Data management {26}

A data management plan (DMP) has been developed at Umeå University using DMPonline, a digital service provided by Umeå University Library, in accordance with institutional and funder requirements. The DMP outlines the procedures for data handling, storage, and analysis during the trial period and after it is finalized to ensure compliance with ethical and regulatory standards. It emphasizes the importance of data confidentiality and participant privacy, detailing how personal identifiers will be removed from the datasets before analysis.

Data collection will be carried out by using REDCap [31], as previously stated. REDCap is a secure, web-based software platform designed to support data capture for research studies. Training sessions will be conducted for all personnel involved in data collection and management to ensure that they are familiar with REDCap’s functionalities and the specific protocols of the study. This will include guidance on accurate data entry, adherence to the study timeline, and the importance of maintaining the integrity of the data throughout the research process.

### Confidentiality {33}

This trial will ensure that all participant information remains secure and accessible only to authorized personnel. Access to the data will be strictly regulated, only designated researchers are allowed to analyze the data for future studies or reports. Any publication resulting from this research will focus on aggregated findings, ensuring that no individual participant’s information is disclosed or can be inferred.

The processing of personal data will be carried out in accordance with the General Data Protection Regulation (GDPR). Participant data will be pseudonymized and stored in the REDCap system. The trial investigators will access REDCap through the Umeå University server using multifactor authentication for data collecting. Participant code numbers will be stored separately in a locked safe at the Department of Clinical Science, Unit for Speech-Language Pathology, Umeå University. FEES assessments will be stored on a secured server at Umeå University, Department of Clinical Science.

## Statistical methods

### Statistical methods for primary and secondary outcomes {27a}

The primary endpoint will be analyzed using an ordinal regression (proportional odds) model, adjusting for baseline DOSS [18, 19] as well as for the stratifying variables center and aspiration. The choice of using random or fixed effects for center is yet to be determined depending on the number of centers that will be recruited. A statistical analysis plan will be established before data retrieval, predetermining details on the analyses.

Further, nutritional status [23], swallowing-related quality of life [24], Barthel index [27], and mRS [28], all variables on ordinal scale, will be analyzed using ordinal regression, adjusted for baseline values, while group differences in the rate of aspiration pneumonia will be tested using negative binomial regression.

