**Methods:**

This national, multicenter, investigator-initiated, randomized, parallel-group trial compares the effect of oral neuromuscular training versus standard care in patients with post-stroke dysphagia. We will enroll 336 consecutive participants who have no prior history of dysphagia and exhibit persistent dysphagia 3 months following the onset of ischemic stroke or intracerebral hemorrhage. Participants will be randomly assigned in a 1:1 ratio to receive either a 12-week intervention consisting of standard routine care combined with oral neuromuscular training (using an oral device with sensors for adherence feedback) or current routine care alone. Standard routine care includes compensatory strategies such as bolus modification, adapted swallowing postures, and maneuvers. The primary outcome is the degree of dysphagia at end of intervention, assessed with Flexible Endoscopy Evaluation of Swallowing (FEES) by blinded evaluators, and analyzed with ordinal regression models. Secondary outcomes are changes in nutritional status, pneumonia, mortality, and quality of life after a 12-week intervention and at 6-month follow-up.

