### Eligibility criteria for participants {14a}

Eligibility criteria are consecutive patients with stroke (ischemic or hemorrhagic) with persistent dysphagia (defined as Dysphagia Outcome Severity Scale, DOSS, ≤5 on FEES assessment) [18, 19] at 1–3 months (4–12 weeks) post-stroke onset. Exclusion criteria: previously known dysphagia; unable or unwilling to give informed consent or to cooperate. The study inclusion and procedure are depicted in Fig. 1.

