### Who will take informed consent? {32a}

Trained investigators at each site will introduce the trial to patients at the standard FEES assessment at 1–3 months post-stroke, providing them with written information about the study. Subsequently, the investigators will facilitate discussions about the trial, giving patients the opportunity to ask questions and seek clarification on the provided materials. The investigators will be certified in Good Clinical Practice (GCP) [20] and the Declaration of Helsinki [21].

For patients with aphasia or those unable to write after a stroke, verbal consent will be sought for participation, as witnessed by an independent observer such as a staff member, relative, or friend, who will then sign and date the form.

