### Ancillary and post-trial care {34}

No formal post care provision is planned in the study. Participants with persistent dysphagia at follow-up 6-month post-intervention (i.e., 12 months post-stroke) will be treated according to the clinical routine at each site.

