### Participant timeline {18}

A schematic diagram of participant enrollment, interventions, assessments, and visits for participants is presented in Fig. 3. Each participant is involved for approximately 9 months (12 weeks intervention and 6 months follow-up period) (see Fig. 3). As a standard procedure, and according to national stroke guidelines, all patients with dysphagia in the acute phase of stroke are followed up with a FEES at 1–3 months after stroke onset. If persistent dysphagia is present, the patient is invited to participate in the study. After their written informed consent is obtained, the participant will be allocated to either intervention or control group. Based on the baseline FEES assessment (performed prior allocation, as part of routine procedure), the participant will receive individualized compensatory strategies. Assessments regarding secondary outcomes will be conducted after the participants have given their informed consent. Same assessments as at baseline are performed after 12 weeks (end-of-treatment) and 6 months later (follow-up). The first participant was enrolled on 26 February 2022, and the final participant is expected to be enrolled in July 2028, based on an estimated annual enrollment rate of 84 participants for the remaining study period.

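### The primary model leaves out time since stroke, age and stroke severity, which gives up some precision although entry spans 4 to 12 weeks; the stated entry times also need reconciling

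*Protocol article*

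**What the plan says.** **Primary model.** Statistical methods {27a} specifies a proportional odds model for DOSS at end of treatment, adjusted for baseline DOSS "as well as for the stratifying variables center and aspiration". For this model it leaves one named choice open, fixed or random effects for center. A SAP is to settle analysis details before data retrieval.

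**Entry window.** Eligibility {14a} requires persistent dysphagia (DOSS of 5 or less) "at 1–3 months (4–12 weeks) post-stroke onset". The consent section {32a} and the participant timeline {18} agree: "at the standard FEES assessment at 1–3 months post-stroke" and "are followed up with a FEES at 1–3 months after stroke onset".

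**Passages that do not match.** The abstract describes participants who "exhibit persistent dysphagia 3 months following the onset of ischemic stroke or intracerebral hemorrhage". Ancillary and post-trial care {34} dates the last visit as "follow-up 6-month post-intervention (i.e., 12 months post-stroke".

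**Availability of the other variables.** Section {25a} states: "Data regarding stroke severity and type will be collected". Age is needed for the age subgroup in {27d}. The onset date is needed to apply the eligibility window.

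**The concern.** Two people with the same baseline DOSS, one at week 4 and one at week 12, may be at different points of natural recovery. Their end-of-treatment assessments fall at about week 16 and week 24 after stroke. Baseline DOSS records present severity but not how long the deficit has lasted.

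The protocol itself expects substantial change without training. Everyone enters with DOSS of 5 or less, yet the sample size section expects only 65% of controls to be in that range at follow-up, so about 35% are expected to leave it. Variables that help predict who recovers would sharpen the treatment comparison.

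What is at stake is precision in the primary analysis. A lesser matter is that a reader of the abstract alone would misjudge how early participants can enter.

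**Working it through.** **Inputs.** From Sample size {19}: odds ratio 2; DOSS distribution 3, 7, 10, 13, 24, 30 and 13% for scores 1 to 7; 135 subjects for 90% power; 168 per group after 20% dropout. Two-sided alpha of 0.05 is an assumption, because the article does not state it.

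**Step 1: reproduce the plan's figure.** Whitehead's formula for 1:1 allocation:

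- Sum of cubed proportions = 0.0466, so 1 − Σp³ = 0.9534.
- N = 12 × (1.960 + 1.2816)² / [(ln 2)² × 0.9534] = 275.3, or 138 per group, against 135 stated (about 2% apart).
- At 135 per group, V = 135 × 135 × 270 / (3 × 271²) × 0.9534 = 21.29. Then z = ln 2 × √21.29 = 3.199 and power = Φ(3.199 − 1.960) = 89.2%.
- Taking 135 as the total would give only 61.5%, so it is per group. This agrees with 135 / 0.8 = 168.75 against the stated 168 per group.

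The plan's figure is reproduced. It is computed on a marginal odds ratio of 2, so it does not rely on any covariate.

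**Step 2: gain from further covariates.** The documents give no prognostic strength, so a range is assumed. R² is the further share of latent outcome variance explained. The linear approximation is power = Φ(3.199/√(1 − R²) − 1.960), and the equivalent increase in sample size is 1/(1 − R²) − 1.

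| Assumed R² | z | Power | Equivalent extra patients |
|---|---|---|---|
| 0 | 3.199 | 89.2% | none |
| 5% | 3.282 | 90.7% | 5% |
| 10% | 3.372 | 92.1% | 11% |
| 15% | 3.469 | 93.4% | 18% |

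**Step 3: check on the proportional odds scale.** In this model adjustment does not shrink a residual variance. It moves the odds ratio away from 1 and slightly lowers the information. Take a normal prognostic score with SD = √[R²/(1 − R²) × π²/3] on the log-odds scale, and hold the marginal odds ratio at 2. The conditional odds ratio is found by averaging over the score. The factor 1 − Σp³ is averaged over the score in the same way, and V = 22.33 × that factor.

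| Assumed R² | SD | Conditional OR | Averaged 1 − Σp³ | Power |
|---|---|---|---|---|
| 5% | 0.42 | 2.03 | 0.950 | 90.5% |
| 10% | 0.61 | 2.07 | 0.945 | 91.7% |
| 15% | 0.76 | 2.11 | 0.941 | 92.9% |

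The linear figures are slightly optimistic, by at most about half a percentage point.

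**Step 4: visit timing.** With 12 weeks of treatment, 6 months of follow-up and 4.345 weeks per month:

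- Entry at week 4: 16/4.345 + 6 = 9.7 months after stroke.
- Entry at week 12: 24/4.345 + 6 = 11.5 months after stroke.

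Twelve months post-stroke therefore fits, in round figures, only the late end of the window.

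**The case against.** The strongest reply is that baseline DOSS plus both stratification factors is a standard prespecified model, so a longer covariate list is a preference and not a correction. Much of that stands. Nothing in {27a} is wrong or self-contradictory.

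Several stronger readings are tempting, and the documents do not support them:

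- **That the comparison is biased, or that a chance imbalance in time since stroke would pass as a training effect.** Allocation is randomised 1:1 and stratified. The error rate of the test already allows for chance imbalance.
- **That the trial is underpowered because of the omission.** Power was set on a marginal odds ratio, and the planned adjustment already adds to it. What is lost is an additional gain.
- **That no analysis uses these variables.** Age group enters a subgroup interaction model ({27d}). Confounders for the per-protocol analysis ({27b}) and covariates for imputation ({27c}) are left to the SAP, which is not shown.
- **That the background figures prove strong recovery inside the entry window.** The fall from over 50% to 17% occurs by day 28, so essentially before the earliest entry. The later change, from 17% to 10–15% at 6 months, is modest. It comes from separate sources on stroke patients generally and says nothing about prognosis given baseline DOSS.
- **That there are two target populations.** Eligibility, consent and timeline agree on 1 to 3 months. Only the abstract states 3 months outright. The post-trial care section implies it through a parenthesis on which no analysis depends.

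Two further cautions stand. The article gives neither instrument nor timing for stroke severity, and the onset date is implied by the eligibility window but not listed as a data item.

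The appeal to an unseen SAP does not fully answer the point. The article states the primary covariate set, and leaves open for it only how center is handled. Its sample size section also accepts that conditioning on baseline variables should add power.

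**Conclusion.** The point holds as an inexpensive improvement, not as an error. The stated primary model omits three plausibly prognostic baseline variables although entry spans 4 to 12 weeks. Validity, type I error and stated power are unaffected.

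The forgone gain is about 1 to 4 percentage points of power from a base of 89.2% at 135 per group, equivalent to about 5 to 18% more patients on the linear approximation. This rests on an assumed 5 to 15% of further latent variance explained beyond baseline DOSS, center and aspiration, on two-sided alpha of 0.05, and on the plan's DOSS distribution. If baseline DOSS already captures most of the prognosis, the gain is near zero.

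The discrepancy in entry and visit times is real but editorial.

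**What to change.** 1. **Primary model.** Before data retrieval, and before the efficacy interim analysis that uses the same model, prespecify weeks from stroke onset to randomization, age and stroke severity as recorded at baseline as additional covariates. Keep them continuous where possible. Name the severity instrument and when it is scored, which must be before randomization. Confirm that the onset date is captured.
2. **Imputation.** Consider the same three variables for the imputation model that the SAP will specify.
3. **Wording.** Reconcile the abstract and Ancillary and post-trial care {34} with Eligibility {14a}, consent {32a} and timeline {18}. Under the 1 to 3 month window, the last visit falls at about 9.7 to 11.5 months post-stroke.

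**Cost.** About three degrees of freedom if each variable enters as one linear term. The reported odds ratio becomes conditional on more covariates; over the assumed range, a marginal 2 corresponds to a conditional 2.03 to 2.11. No new assessments should be needed, provided severity and onset date are recorded as the article indicates or implies.

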#### Secondary outcomes

The intervention and the control group will be compared at end-of-treatment and at 6-month follow-up, adjusted for baseline values on the following secondary outcomes:Nutritional status [23] is measured with the Mini Nutritional Assessment Short Form (MNA-SF). The MNA-SF contains 6 items with a total score ranging from 0 to 14; a score of ≥12 points indicate that a person is well-nourished, 8–11 points indicate a risk of malnutrition, and <7 points indicate that the person is malnourished. MNA has been shown to have high sensitivity and specificity (96% and 98%, respectively) and significant agreement between observers (*K* = 0.51) and the MNA-SF has been shown to be a stand-alone nutritional assessment. The total score will be analyzed as an ordinal variable without categorization and compared between group.Swallowing-related quality of life is measured with the Swallowing Quality of Life Questionnaire (SWAL-QOL) [24], which is a patient-reported outcome measure (PROM) and consists of 44 items on a 5-point Likert scale that assesses 10 quality-of-life concepts: burden, eating duration, eating desire, food selection, communication, fear, and mental health. It further contains a dysphagia clinical symptom scale (symptom score). Scores for each domain are calculated using a linear transformation to a total test score ranging from 0 to 100, with higher scores indicating better quality of life. The Swedish version of SWAL-QOL has high internal consistency, high validity, and excellent test-retest reliability. The total score will be treated and analyzed as an ordinal variable without categorization and compared between groups.Rate of aspiration pneumonia based on the modified criteria by Centers for Disease Control and Prevention (CDC) for stroke-associated pneumonia [25]. The data are collected through patient reports and records. The incidence of aspiration pneumonia will be compared between groups.Lip force [26] assessed with a device measuring the lip force in newton (N). The maximum value (best of three trials) will be treated as a continuous variable and compared between groups.Functional status measured with (a) the Barthel index (BI) [27] which is an ordinal scale that consists of 10 items measuring a person’s functional independence on activities in daily living (ADL): bowels, bladder, toileting, bathing, eating, dressing, grooming, transfer, stairs, and ambulation. The scale ranges from 0 to 100. BI is widely used within both stroke care and research, and it is sensitive enough to detect improvement in function after stroke as well as having good reliability between administrators. Functional status is also measured by (b) the modified Rankin Scale (mRS) [28], which is a 7-point scale ranging from 0 (no symptoms) to 6 (death). The mRS has shown high validity and reliability when tested among patients with stroke. BI and mRS total scores will be analyzed as ordinal variables without categorization and compared between groups.Death: The mortality rate will be compared between groups.

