### Sequence generation: type of randomization {21b}

The allocation sequence was created centrally using computer-generated random numbers stratified for center and penetration-aspiration (yes/no) according to the Penetration Aspiration Scale (PAS) [30], allocating eligible patients in a 1:1 ratio to intervention or control group. Permuted blocks with random block sizes will be used.

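### The secondary models are specified without the randomisation strata that the primary model includes, so their tests may be somewhat conservative

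*Protocol article*

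**What the plan says.** Section {21b} of the protocol article describes randomisation "stratified for center and penetration-aspiration (yes/no) according to the Penetration Aspiration Scale (PAS"), with 1:1 allocation. It adds that "Permuted blocks with random block sizes will be used".

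Section {27a} gives the primary proportional odds model as "adjusting for baseline DOSS [18, 19] as well as for the stratifying variables center and aspiration". For MNA-SF, SWAL-QOL, Barthel index and mRS, the same section then says: "all variables on ordinal scale, will be analyzed using ordinal regression, adjusted for baseline values, while group differences in the rate of aspiration pneumonia". The sentence closes by giving pneumonia a negative binomial model, with no covariate named.

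The Secondary outcomes section makes one general statement, that the groups will be compared "adjusted for baseline values on the following secondary outcomes". Aspiration pneumonia is in the list that follows.

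Section {27a} also says that a SAP will fix analysis details before data retrieval. That SAP is not shown.

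**The concern.** Two adjustment sets are stated. The primary model has baseline plus strata; the secondary models have baseline. No reason is given for the difference, and the sample size section {19} argues that conditioning on baseline DOSS, center and aspiration should add power. That reasoning carries over to the secondary outcomes.

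Blocking within strata nearly balances the arms on center and aspiration. If those factors are prognostic, the balance removes part of the sampling variation of the treatment effect. A model without them does not register this, so its standard error is too large. The test then rejects too rarely under the null and has less power under the alternative.

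At stake is precision on nutrition, swallowing-related quality of life, function and pneumonia, the outcomes through which the Discussion expects better swallowing to benefit patients. Pneumonia is the least clearly specified. Baseline adjustment has no obvious meaning for an incident event, and baseline penetration-aspiration, a plausible predictor, is already recorded for randomisation.

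**Working it through.** **The plan's own figure.** The article gives no power for secondary outcomes, so the primary sample size is the only figure to reproduce. Inputs from {19}: OR 2, power 90%, DOSS distribution 3, 7, 10, 13, 24, 30 and 13%. Two-sided alpha 0.05 is assumed, because none is stated.

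- Formula: N = 12(z_a + z_b)² / [ln(OR)² (1 − Σp³)].
- Σp³ = 0.046588, so 1 − Σp³ = 0.953412.
- N = 12 × (1.960 + 1.282)² / (0.4805 × 0.9534) ≈ 275.3, or about 138 per group against the stated 135. Power at 270 is 89.2%.
- Dropout: 135 / 0.8 = 168.75, against the stated 168.

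The figures reproduce closely if 135 is read as per group. As a total, 135 would give 61.5% power.

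**Ordinal secondary outcomes.** Two models were compared by simulation: treatment plus baseline value, and the same plus aspiration and fixed center effects.

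- From the article: 270 analysed (2 × 135), nine centers, 1:1 stratified permuted blocks, OR 2, and the DOSS distribution as a stand-in for a seven-level outcome.
- Assumed: blocks of 4 or 6, 50% aspiration, baseline coefficient 1.0 per SD on the log-odds scale, baseline-aspiration correlation parameter 0.4, and the strata effects below.
- 1,500 replicates. Monte Carlo standard error is about 0.6 points for type I error and 0.8 to 1.1 points for power.

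| Residual strata effect (log-odds scale) | Type I error, baseline only | Type I error, baseline + strata | Power, baseline only | Power, baseline + strata |
|---|---|---|---|---|
| None | 4.3% | 4.7% | 87.7% | 88.1% |
| Center SD 0.5, aspiration 0.5 | 4.9% | 6.1% | 86.6% | 88.4% |
| Center SD 1.0, aspiration 1.0 | 2.9% | 5.5% | 77.9% | 87.3% |

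The power losses are 0.4, 1.8 and about 9 points. A shorter run (300 replicates, standard error about 2 points) at center SD 0.5 and aspiration 1.0 gave 82.3% against 87.7%, with type I error of 5.0% and 4.7%. The 6.1% is within two Monte Carlo standard errors of 5%.

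**Pneumonia.** This was approximated, not simulated. Let f be the share of outcome variance lying between strata. With the arms balanced on the strata and no covariates in the model, type I error ≈ 2Φ(−1.96/√(1−f)). Where full adjustment gives 80% power, the unadjusted power ≈ Φ(2.80 − 1.96/√(1−f)). The article gives no pneumonia rate, so the inputs are assumed: 0.1 to 0.4 events per patient, aspiration rate ratio 2 to 4, center SD 0.3 to 0.5 on the log scale, 50% aspiration, dispersion 1.

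- Low end: between-strata variance 0.0022 of a total 0.1143, f = 0.019. Type I error 4.8%, power 79.5%.
- High end: 0.119 of 0.799, f = 0.149. Type I error 3.4%, power 75%.

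**The case against.** The strongest objection is that this is detail for the SAP. The article never says that the strata are excluded, it defers analysis details, and even the form of center in the primary model is left open. This stands in part. A reader might infer that the trial has decided to discard the strata, and the text does not support that. But the article is not silent on secondary covariates. It states them in two sections, each time without the strata, and a SAP that follows those statements would leave them out.

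A reader might also infer that the secondary p-values will be wrong. That depends on how prognostic center and aspiration remain once the outcome's own baseline is in the model, and the article gives no figure for this. Simulating without a baseline covariate makes the effect look larger: type I error 4.1% to 2.4%, and power 66.5% to 59.8% against about 70%, at an assumed OR of 1.7 with 269 patients. That is not the model the plan describes.

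Nor is it right to say that pneumonia gets no adjustment at all. The general statement under Secondary outcomes covers it, although {27a} names no covariate and it is unclear which baseline value is meant.

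Finally, full center adjustment could be unstable in a count model with few events and nine or more sites. That is correct, and it limits what should be asked of the pneumonia model.

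**Conclusion.** The point holds in a limited, conditional form. As written, the secondary ordinal models omit the stratification factors that the primary model includes, and the pneumonia model's covariates are unclear. If the strata are prognostic beyond baseline, the secondary tests are conservative. The power cost is about 0 to 2 points with no or moderate residual effects and up to about 9 points with strong ones. Type I error is clearly below nominal only in the strong case. These sizes rest on assumed strata effects, a seven-level outcome and a secondary effect as large as OR 2; the pneumonia figures are rougher still. Direction and wording are secure; magnitude is not. The primary analysis already includes both strata, no false positives are created, and the article claims no power for secondary outcomes. This is a minor point, worth making because the remedy is cheap.

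**What to change.** In {27a}, and in the matching sentence under Secondary outcomes, state that the models for MNA-SF, SWAL-QOL, Barthel index and mRS adjust for the outcome's baseline value plus center and baseline penetration-aspiration, with center in the same form as in the primary model. State that the negative binomial model for pneumonia includes at least baseline penetration-aspiration, with center as a random effect, or with small centers pooled, if events are sparse. Carry the same wording into the SAP before data retrieval.

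The cost is wording only, since both factors are already held in the randomisation record. With nine fixed center effects the models gain 1 + 8 = 9 coefficients; with a random center effect they gain one coefficient and one variance. In the simulation with no residual strata effect, the extra terms cost no power (88.1% against 87.7%).
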